### 2.17. Sample Size and Statistical Analysis

With reference to data from previous studies published in relevant journals, a total of 60 PD patients are proposed to be enrolled in this single center study. The sample size of this study was calculated based on the improvement in the UPDRS scale after 28 weeks of treatment and differences between groups. Calculations are performed using PASS (Power Analysis and Sample Size) 2008 software (UT, OH, USA), assuming a four-point reduction in the UPDRS at the end of treatment in A1, a five-point reduction in A2, a two-point reduction in S1, and a four-point reduction in S2, with a standard deviation of 2, a test level of 0.05, and a degree of certainty of 0.9 yielded for 13 subjects per group. Considering that the patient dropout rate may be about 10% [24,40], the final plan is to enroll n = 15 cases in each group for n = 60 cases in total. The minimum sample size required to meet the hypothesis of this clinical study is 60, and actual samples of 60 cases or more are in accordance with the clinical study design principles and statistical requirements.

Statistical analysis applies SPSS 20.0 for processing; MRI, EEG, and EMG data are processed on MATLAB platform (Math Works Inc., Natick, MA, USA). All statistics are performed using two-sided tests, and α = 0.05 is the cut-off point used to decide whether the hypothesis is statistically significant. Between-group comparisons of quantitative data will be performed using analysis of variance (ANOVA) or Wilcoxon rank sum test depending on the distribution of the data. A paired *t*-test or Wilcoxon signed-rank test will be used for comparison before and after treatment. Categorical data are tested by chi-square test or exact probability method (if the chi-square test is not applicable).

To compare the changes in UPDRS scores before and after the iTBS intervention at each time point, mainly comparing the differences in their means, two-way repeated-measures ANOVA was used to compare the main effects and the interaction effects between the two for different groups and follow-up points (baseline, week 14, week 28), and post hoc analysis was performed using the Bonferroni test to compare the differences between each follow-up point and baseline scores.

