### 2.2. Study Design

NET-PD is a 2-year prospective single-center, double-blind, multi-arm, delayed-start, sham-controlled trial. The study is conducted in two stages—the pseudo-controlled and active-treatment stage—with each stage consisting of a 2-week intensive phase and a 12-week maintenance phase, for a total of 14 weeks. The intensive period involves daily or twice-daily iTBS (or pseudo-stimuli) per week, for a total of 10 or 20 sessions, and the maintenance period consists of 12 weeks of iTBS (or pseudo-stimuli) once or twice a day, 2 days a week, for a total of 24 sessions in the single-stimulation group or 48 in the double group. In stage 1 (pseudo-controlled stage), patients are randomly assigned to one of four intervention groups in a 1:1:1:1 ratio: early-start single iTBS group (A1), early-start double iTBS group (A2), delayed-start single iTBS group (S1), and delayed-start double iTBS group (S2). The early-start groups conduct active iTBS throughout, whereas the delayed-start groups use pseudo-stimuli in the first stage and start using iTBS in the second stage. The only difference between the single- and double-stimulation group is the number of sessions per day: once daily for the single group and twice daily for the double group. In stage 2 (active treatment stage), participants in A1 and A2 continue to receive the same iTBS protocol as the first stage, while those in S1 and S2 start to receive active iTBS. All patients are required to have a detailed follow-up clinical assessment and electrophysiology record at baseline, 2 weeks, 14 weeks, 16 weeks, and 28 weeks. MRI and peripheral blood are collected at baseline, 14 weeks, and 28 weeks (Figure 1, Table 1). Each patient will spend 7 months in this study and the total duration of the research will be approximately 2 years, from July 2022 (first in) to December 2024 (last out) (Figure 2).

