### 2.15. Outcome Measures

According to the results of previous large delayed-start design disease-modifying drug studies, the neuroprotective effect can be commonly reflected by the difference in the changes in the UPDRS score before and after treatment between groups [22,39]. In an NET-PD study, the primary outcome is the differences in changes in UPDRS scores in the four groups before and after the iTBS intervention. As a secondary outcome, we will evaluate the effects of iTBS treatment on clinical symptoms, motor symptoms such as gaiting and postural balance, and non-motor symptoms such as mood, cognition, olfaction, and sleeping condition in PD patients. As a neuro-modulation intervention study, EEG, EMG and MRI images can also be visualized to indicate the functional activity status of the brain. The safety of the treatment will be assessed using a self-administered side effect scale. Additionally, self-administered side effects scales will be used to assess iTBS safety.

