### 2.16. Study Hypothesis

Firstly, UPDRS scores are expected to be significantly lower in group A1 and A2 than in group S1 and S2 after stage 1, and the scores show a trend from low to high in groups A2, A1, S2, and S1 after stage 2. Next, the change in the slope of the weekly UPDRS scores will be compared among the 4 groups. We expect a slower rate of deterioration (i.e., increase in UPDRS scores) with the iTBS intervention than with the pseudo-stimulation group. The mean total UPDRS score deteriorates less from baseline to week 28 in the early-start groups than in the delayed-start groups. For the changes in slope of UPDRS scores between weeks 14 and 28, the early-start groups are expected to respond better than the delayed-start groups.

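### The rank-based alternative to ANOVA is a two-sample test, so it cannot make the four-group comparisons this trial needs

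*Protocol article*

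**What the plan says.** Section 2.2 sets up four parallel arms: "patients are randomly assigned to one of four intervention groups in a 1:1:1:1 ratio". They are early-start single (A1), early-start double (A2), delayed-start single (S1) and delayed-start double (S2). Section 2.15 defines the primary outcome across all of them: "the primary outcome is the differences in changes in UPDRS scores in the four groups before and after the iTBS intervention". Section 2.16 contains an early-versus-delayed hypothesis, "UPDRS scores are expected to be significantly lower in group A1 and A2 than in group S1 and S2 after stage 1", and a four-group one, "the change in the slope of the weekly UPDRS scores will be compared among the 4 groups".

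Section 2.17 gives a general rule for quantitative data: "Between-group comparisons of quantitative data will be performed using analysis of variance (ANOVA) or Wilcoxon rank sum test depending on the distribution". It sets one significance level throughout: "All statistics are performed using two-sided tests, and α = 0.05 is the cut-off point".

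A separate paragraph of the same section covers UPDRS. It names a two-way repeated-measures ANOVA with group, time and their interaction, followed by the only multiplicity adjustment in the article: "post hoc analysis was performed using the Bonferroni test to compare the differences between each follow-up point and baseline scores".

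**The concern.** The general rule pairs a test for any number of groups with a test for exactly two, and it lets the observed distribution choose between them. For a four-group comparison the two branches do not answer the same question. ANOVA asks once, at 5%, whether any arm differs. The rank sum test can only take two samples, so an analyst who follows the sentence for a four-group question must compare arms in pairs.

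The Bonferroni step does not help here. It is attached to comparisons over time, follow-up against baseline, and not to comparisons between arms. As written, the article gives each arm-against-arm rank sum test the common level of 0.05.

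The outcomes exposed are mainly those without a model of their own: the balance, mood, cognition, sleep, olfaction, autonomic and quality-of-life scales of section 2.14. These are rating-scale scores in arms of 15, so the non-normal branch may well be used. At stake is whether a claimed difference between arms on such a scale carries a 5% error rate or a considerably larger one.

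**Working it through.** **Inputs.** Four arms, 1:1:1:1 (section 2.2). Two-sided level 0.05; 13 per arm for analysis and 15 enrolled; assumed UPDRS reductions of 4 (A1), 5 (A2), 2 (S1) and 4 (S2); SD 2; power 0.9; dropout about 10% (all section 2.17).

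**Step 1: the plan's own figure.** The sample size starts from "assuming a four-point reduction in the UPDRS at the end of treatment in A1, a five-point reduction in A2, a two-point reduction in S1" and four points in S2. Treat it as a one-way four-group F test.
- Mean reduction = (4 + 5 + 2 + 4)/4 = 3.75.
- Sum of squared deviations = 0.25² + 1.25² + 1.75² + 0.25² = 0.0625 + 1.5625 + 3.0625 + 0.0625 = 4.75.
- Noncentrality λ = n × 4.75 / 2² = 1.1875n.
- n = 12: λ = 14.25, df 3 and 44, power 0.872.
- n = 13: λ = 15.4375, df 3 and 48, power 0.901.
- Dropout: 13/0.9 = 14.4, rounded up to 15 per arm, 60 in total.

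The stated 13 and 15 per arm reproduce. The trial is sized on one global four-group test.

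**Step 2: number of pairs.** Four arms give 4 × 3 / 2 = 6 pairs. If six tests at 0.05 were independent, the chance of at least one false positive would be 1 − 0.95⁶ = 0.265. Pairs share arms, so the tests are correlated and the true figure is lower. It was therefore simulated.

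**Step 3: simulation under no difference.** Four normal samples of 13 or 15, with two-sided tests at 0.05. The figure is the chance of at least one p-value below 0.05.

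| Procedure | 13 per arm | 15 per arm |
|---|---|---|
| Six unadjusted rank sum tests, exact or continuity-corrected p-values | about 19% | about 19% |
| Same, without continuity correction | about 21% | about 21% |
| Kruskal-Wallis, one test | about 5% | about 5% |
| One rank sum test, A1+A2 against S1+S2 | about 5% | about 5% |
| Six rank sum tests at 0.05/6 = 0.0083 each | about 4% | about 3% |

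The 19% and 21% differ only by the continuity correction. If only the four early-against-delayed pairs were tested, the figure is about 15% to 17%. For two independent contrasts it is 1 − 0.95² = 0.0975, about 10%.

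**Step 4: the price of adjustment.** This uses t-test power with the plan's SD of 2, as a guide only, because the plan gives no effect sizes for the secondary scales.

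| Difference between two arms | Level | 13 per arm | 15 per arm |
|---|---|---|---|
| 2 points (A1 against S1) | 0.05 | 69% | 75% |
| 2 points (A1 against S1) | 0.05/6 | 39% | 47% |
| 1 point (A2 against S2) | 0.05 | 23% | 26% |
| 1 point (A2 against S2) | 0.05/6 | 7% | 9% |

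**The case against.** **The primary outcome has its own model.** UPDRS is assigned a repeated-measures ANOVA, and no rank-based switch is attached to it. This stands. A reader might infer from the general rule that the primary analysis changes tests when the data look non-normal. The article does not say so, and the more natural reading is that the rule serves baseline and secondary variables.

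**Six pairwise tests are an assumption.** This also stands. Nowhere does the article say that all pairs will be tested. A reader might go further and conclude that the rank sum test could only be run as six pairwise comparisons. That is not so: several hypotheses in section 2.16 set early start against delayed start, and once those arms are pooled the rank sum test is valid and holds its 5% level. Section 2.16 also has a comparison among all four groups, however, so the need for a four-group test remains.

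**The name may be shorthand for rank-based tests in general.** The sample size shows that the authors had a global test in mind, which gives this some plausibility. But nothing in the text says it, no rank test for more than two groups is named, and the test that is named cannot do the job.

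**Between-arm multiplicity control may be in an analysis plan that is not shown.** This is partly right. The absence of such control is not the finding. The finding is that the test stated here is the wrong kind; the scope of the Bonferroni step matters only because it shows that the article's own adjustment does not repair the consequence.

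**Conclusion.** The point holds as an error in a stated method. Section 2.17 gives a two-sample test as the alternative to ANOVA in a four-arm trial, and that test cannot make a four-group comparison.

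The size is conditional. The familywise error is about 19%, against about 5% for Kruskal-Wallis, if the rank-based branch is taken, all six pairs are tested, and each is judged at 0.05 without adjustment. With fewer pairs it is smaller, and with the pooled contrast alone there is no inflation. How often the rank-based branch would be taken cannot be judged from the article.

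The consequence falls mainly on the secondary quantitative outcomes. Neither the sample size nor the repeated-measures ANOVA named for UPDRS is affected.

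**What to change.** In section 2.17, name the Kruskal-Wallis test as the rank-based alternative to ANOVA for comparisons of the four arms. Add that it is followed by pairwise rank sum tests with Holm or Bonferroni adjustment over the pairs tested. Allow an unadjusted rank sum test only for a pre-specified pooled contrast of A1 and A2 against S1 and S2.

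This takes a sentence or two and changes neither the sample size nor the conduct of the trial. Section 3 reports two patients enrolled at the time of writing, so the wording could be settled before outcome data bear on it. The downside is lower power for individual pairs, on the scale shown in the working. Holm loses no more than Bonferroni, and the pooled contrast is not affected.

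### The UPDRS model counts baseline as an outcome visit, does not say which term tests the primary outcome, and no between-group comparison adjusts for baseline

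*Protocol article*

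**What the plan says.** Section 2.15 of the protocol article defines the primary endpoint as a comparison of changes: "the primary outcome is the differences in changes in UPDRS scores in the four groups before and after the iTBS intervention".

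Section 2.17 gives the UPDRS model: "two-way repeated-measures ANOVA was used to compare the main effects and the interaction effects between the two for different groups and follow-up points". The levels listed for the time factor are baseline, week 14 and week 28, so baseline is one of the outcome visits. The Bonferroni post hoc tests compare each follow-up visit with baseline, not one arm with another.

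For other quantitative data the same section says "Between-group comparisons of quantitative data will be performed using analysis of variance (ANOVA) or Wilcoxon rank sum test"; the choice is to follow the distribution. It does not say whether raw follow-up scores or changes are compared. No covariate is named for any between-group comparison.

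The sample size for week 28 was derived by "assuming a four-point reduction in the UPDRS at the end of treatment in A1, a five-point reduction in A2, a two-point reduction in S1"; for S2 the figure is four points. The calculation was run "with a standard deviation of 2, a test level of 0.05, and a degree of certainty of 0.9 yielded for 13 subjects per group". The article does not say whether the SD is that of the change or of the score.

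**The concern.** Main effects and interaction are both to be read, and neither is named as the test of the primary outcome.

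- **Group main effect.** This compares arm averages over all three visits. At baseline, the day of randomisation in Table 1, the expected difference between arms is zero, so the main effect is two thirds of the mean post-treatment difference. It also carries the full between-patient spread, which a change score largely removes. It does not answer the question set in section 2.15.
- **Group-by-time interaction.** This does compare changes, but over all arms and visits at once. A significant result does not say at which visit or between which arms the difference lies. The stated post hoc tests do not settle that, because they are not between-arm contrasts.
- **Unused baseline.** UPDRS and most secondary scales have a pre-treatment value in Table 1. With 13 evaluable patients per arm, leaving it out gives up precision and leaves chance baseline differences in the comparison.

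**Working it through.** **Inputs from section 2.17.** Mean reductions are 4, 5, 2 and 4 (A1, A2, S1, S2), SD 2, α = 0.05 and 13 per arm.

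**Assumptions not in the documents.**
- SD 2 is the SD of change.
- All visits have equal variance σ² and equal pairwise correlation r (compound symmetry), with r = 0.5, 0.7 or 0.9.
- Week-14 differences between arms are a fraction f of those at week 28, with f = 0.5 or 1.

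**1. The plan's own figure.** The mean of the four reductions is 3.75. The sum of squared deviations is 0.0625 + 1.5625 + 3.0625 + 0.0625 = 4.75. For a one-way ANOVA, λ = n × 4.75 / 4. At n = 13, λ = 15.44 and power is 0.901; at n = 12 it is 0.872. So 13 per arm is reproduced, as an unadjusted four-group comparison of change.

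**2. Variance of a single score.** From 2σ²(1 − r) = 4, σ² = 2/(1 − r) = 4.00, 6.67 and 20.0 at r = 0.5, 0.7 and 0.9.

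**3. Group main effect with baseline as a level.** The effect is (0 + f + 1)/3 of the week-28 effect. The variance of a three-visit mean is σ²(1 + 2r)/3. Hence λ = 13 × 4.75 × [(1 + f)/3]² / variance, on 3 and 48 df.

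| r | variance | λ, f = 0.5 | power | λ, f = 1 | power |
|---|---|---|---|---|---|
| 0.5 | 2.67 | 5.79 | 0.47 | 10.29 | 0.74 |
| 0.7 | 5.33 | 2.89 | 0.25 | 5.15 | 0.42 |
| 0.9 | 18.67 | 0.83 | 0.10 | 1.47 | 0.14 |

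**4. Group-by-time interaction.** The interaction sum of squares is 4.75 × [(1 + f²) − (1 + f)²/3], which is 2.375 for f = 0.5 and 3.167 for f = 1. The error variance is σ²(1 − r) = 2 for every r. So λ = 13 × 2.375/2 = 15.44 or 13 × 3.167/2 = 20.58, on 6 and 96 df. Power is 0.83 or 0.93. At f = 0.5, λ equals that of step 1; power falls from 0.90 to 0.83 because the signal is spread over 6 df instead of 3.

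**5. Week-28 ANCOVA on baseline UPDRS.** Residual variance is σ²(1 − r²) = 2(1 + r), which is (1 + r)/2 of the change-score variance.

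| r | residual variance | saving against change | λ | power |
|---|---|---|---|---|
| 0.5 | 3.0 | 25% | 20.58 | 0.97 |
| 0.7 | 3.4 | 15% | 18.16 | 0.94 |
| 0.9 | 3.8 | 5% | 16.25 | 0.92 |

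Unadjusted change has power 0.90 throughout.

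**6. A larger week-14 separation.** If the early arms already had their 4 and 5 points at week 14 and the delayed arms had none, main-effect power is 0.98, 0.76 and 0.26 at r = 0.5, 0.7 and 0.9, and interaction power is above 0.99. The main-effect figures therefore depend heavily on an unstated week-14 pattern.

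**7. Secondary scales.** If changes would have been compared, ANCOVA saves (1 − r)/2 of the variance, 5 to 25% as above. If raw follow-up values would have been compared, it saves r², 25 to 81% over r = 0.5 to 0.9.

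**The case against.** The strongest reply is that the interaction is stated, tests differences in change, and needs baseline as a level to do so; this is a conventional set-up. That stands. A reader might infer from step 3 that the primary analysis has power as low as 0.10. The documents do not support this: they never name the main effect as the deciding test, and the interaction has 0.83 to 0.93 under the same assumptions. At r = 0.9 with equal week-14 differences, the interaction's 0.93 is slightly above the ANCOVA's 0.92.

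Two other strong readings also fail. Arms are randomised 1:1:1:1, so unadjusted change is not biased; chance imbalance is a matter of precision. The sample size is not wrong either, because 13 per arm is reproduced without a covariate.

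The large saving for secondary scales holds only if raw follow-up values are compared, which the text does not say. Side effects have no pre-treatment entry in Table 1, so the covariate point cannot cover every outcome.

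Finally, a condensed article may leave covariates to an analysis plan, and a missing covariate alone would be no finding. But this article does state the model, the levels of its time factor and the terms to be read. What remains is that this stated method leaves the primary test unidentified and uses baseline less efficiently than it could.

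**Conclusion.** The point holds as one of efficiency and of an unnamed primary test. If the group main effect were read as the test, it would address the wrong quantity with power 0.10 to 0.74 over r = 0.9 to 0.5 and the two proportional week-14 patterns. If the interaction were read, power is 0.83 to 0.93 in an omnibus test that does not isolate week 28. Baseline-adjusted analysis at week 28 has 0.92 to 0.97, against 0.90 for unadjusted change, a saving of 5 to 25% of residual variance.

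All of this rests on assumed correlations, compound symmetry and SD 2 being the SD of change. If SD 2 is instead the SD of the score, ANCOVA still has power at least as high as change at every r examined. The change is worth making, but nothing here invalidates the trial.

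**What to change.** In section 2.17:

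- Make UPDRS at weeks 14 and 28 the outcome. Fit a repeated-measures model with group, visit, group-by-visit, baseline UPDRS and baseline-by-visit.
- Name the group comparison at week 28 from that model as the test of the primary outcome. This is the comparison for which the sample size was calculated.
- For each secondary quantitative scale with a pre-treatment value, replace plain ANOVA by ANCOVA with that value as covariate. For MMSE this is the screening value, since Table 1 shows no baseline assessment.

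The cost is analysis wording and one or two degrees of freedom. No visits, data or patients are added. The article reports two patients enrolled, so at that stage the change could still be specified in advance.

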### 2.3. Inclusion Criteria

Patients entering this study are required to meet all of the following criteria:PD diagnosed according to the revised clinical diagnostic criteria of the Movement Disorder Society (MDS) International (2015 version);Aged 50–80, age of diagnostic ≥50, male or female;Hoehn–Yahr stage ≤4;With or without levodopa, maintaining medication stability during the study period;Good compliance with the long-term intervention and follow-up.

Written informed consent should be signed by each patient; this study has been approved by Ruijin Hospital’s ethical committees.

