### 2.14. Baseline Assessments and Follow-Up Evaluations

After screening, all the eligible patients will undergo a comprehensive detailed assessment, including basic demographic, motor and non-motor symptoms, α-syn in the peripheral blood, and resting functional MRI, EEG, and EMG. All the physicians involved in assessment receive consistency training prior to the start of the trial to ensure the uniformity of the standard. Basic demographic information including gender, age, education, concomitant diseases, family history, medication usage, etc. is taken. All motor symptom assessments will be video-numbered and scored by two independent physicians. Various aspects of the patients’ clinical symptoms are measured using Unified Parkinson Disease Rating Scale (UPDRS), Berg Balance Scale (BBS), Hamilton Depression Scale (HAMD), Hamilton Anxiety Scale (HAMA), MMSE, Montreal Cognitive Assessment (MoCA), Pittsburgh sleep quality index (PSQI), 39-item PD Questionnaire (PDQ-39), 16-item odor identification test from Sniffin’ Sticks (SS-16), Scale for Outcomes in Parkinson’s disease for Autonomic Symptoms (SCOPA-AUT), and Wexner constipation scale. At the same time, we draw the patient’s peripheral blood for cytology, biochemistry, and coagulation tests and to detect α-syn in exosomes. After two intensive phases (week 2 and week 16), patients will receive a brief follow-up evaluation including the UPDRS, EMG acquisition and side effects. At midterm (week 14) and the endpoint of the experiment (week 28), the patients must complete the same detailed set of evaluations as the baseline.

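### UPDRS analysis makes baseline a time level, not a covariate, so the week-28 comparison is an unadjusted change score; adjusting is a free but probably small gain

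*Protocol article*

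**What the plan says.** Section 2.15 of the protocol article defines the outcome: "the primary outcome is the differences in changes in UPDRS scores in the four groups before and after the iTBS intervention". The only analysis described for UPDRS change is in section 2.17: "two-way repeated-measures ANOVA was used to compare the main effects and the interaction effects" for "different groups and follow-up points (baseline, week 14, week 28"). Follow-up is by Bonferroni: "post hoc analysis was performed using the Bonferroni test to compare the differences between each follow-up point and baseline scores". No baseline covariate is named. The article does not label this the primary model; that is inferred from its being the analysis given for the primary outcome.

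UPDRS is measured at two further visits. Section 2.14 states: "After two intensive phases (week 2 and week 16), patients will receive a brief follow-up evaluation including the UPDRS". Section 2.2 and Table 1 agree. Neither visit is a level of the stated model.

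Section 2.16 promises more than a comparison of means: "the change in the slope of the weekly UPDRS scores will be compared among the 4 groups". It also states an expectation that begins "For the changes in slope of UPDRS scores between weeks 14 and 28", with early start to do better than delayed start. The sample size in section 2.17 rests on the week-28 change.

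**The concern.** When baseline is one level of the repeated outcome, the group-by-time contrast from baseline to week 28 is the difference between arms in raw change. Baseline UPDRS is already in hand and predicts the week-28 score. Subtracting it uses that information less efficiently than regressing on it, unless the correlation is 1.

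The model also tests a group main effect. That effect averages three visits, and at one of them randomisation makes the expected arm difference zero.

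The three levels do not fit section 2.16 either. A slope from week 14 to week 28 that rests on those two visits alone is just another difference of two scores, although a week-16 score exists.

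At stake are avoidable variance in a 60-patient trial and a slope hypothesis that the stated model does not serve. The validity of the between-arm comparison is not at stake.

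**Working it through.** **1. The plan's own figure.** Inputs from section 2.17: reductions of 4, 5, 2 and 4 points (A1, A2, S1, S2), SD 2, two-sided alpha 0.05, power 0.9.
- The mean is 3.75 and the squared deviations sum to 0.0625 + 1.5625 + 3.0625 + 0.0625 = 4.75.
- For the four-group F test, the noncentrality at 13 per arm is 13 × 4.75 / 2² = 15.4.
- Power is 0.872 at 12 per arm and 0.901 at 13, so 13 per arm reproduces. 13 / 0.9 = 14.4, rounded up to 15 per arm, 60 in all.

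**2. Variance with and without adjustment.** With equal score variance s² at baseline and week 28 and correlation rho:
- change score: 2s²(1 − rho)
- baseline-adjusted: s²(1 − rho²)
- ratio: (1 − rho²) / [2(1 − rho)] = (1 + rho)/2

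**3. Early versus delayed start at week 28.** The assumed difference is (4 + 5)/2 − (2 + 4)/2 = 1.5 points. At 13 per arm its standard error is 2 × √(4 × 0.25/13) = 0.555, and power by noncentral t (48 df) is 75.5%. The next table reads SD 2 as the SD of change. The article gives no rho, so these values are assumed.

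| rho | Variance ratio | Power, 1.5-point contrast | Power, four-group test | n per arm for 90% (four-group) |
|---|---|---|---|---|
| unadjusted | 1 | 75.5% | 90.1% | 13 |
| 0.5 | 0.75 | 86.4% | 96.7% | 11 |
| 0.7 | 0.85 | 82.0% | 94.4% | 12 |
| 0.9 | 0.95 | 77.6% | 91.6% | 13 |

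**4. Which rho is consistent with the plan.** If SD 2 is the SD of change, then 4 = 2s²(1 − rho), so s = √(2/(1 − rho)). That gives s = 2.0, 2.6 and 4.5 points at rho 0.5, 0.7 and 0.9. Section 2.3 admits Hoehn–Yahr stages up to 4 and, on medication, states: "With or without levodopa, maintaining medication stability during the study period". A score SD of 2.0 to 2.6 points is hard to square with such broad entry. Working the other way, with rho = 1 − 2/s²:

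| Assumed score SD | Implied rho | Variance ratio | Power, 1.5-point contrast |
|---|---|---|---|
| 5 | 0.92 | 0.96 | 77.2% |
| 8 | 0.97 | 0.98 | 76.1% |
| 10 | 0.98 | 0.99 | 75.9% |
| 15 | 0.99 | 0.996 | 75.7% |

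The gain over 75.5% is 0.2 to 1.7 points.

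**5. Group main effect.** With expected arm differences 0, d14 and d28, the average over the three levels is (d14 + d28)/3. Over the two post-baseline visits it is (d14 + d28)/2. Including baseline shrinks the signal to two thirds.

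**6. Weeks 2 and 16, week-28 contrast.** The generalised least squares variance of the arm difference (common baseline mean, unstructured visit means) was compared for five visits against three, under compound symmetry and under exponentially decaying correlation, with rho from 0.5 to 0.9. The ratio is 1.000 with complete data and 0.989 to 0.997 with 10% dropout spread evenly over the visits.

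**7. Weeks 2 and 16, slopes.** For a straight line with independent residuals, slope variance is proportional to 1/Σ(t − mean t)².
- Weeks 14–28: 98 without week 16, 114.7 with it; ratio 98/114.7 = 0.855.
- Weeks 0–28: 392 with three visits, 520 with five; ratio 392/520 = 0.754.

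**The case against.** A change score is unbiased over randomisation, and it estimates what section 2.15 asks for. At high rho it is nearly equivalent to the adjusted analysis. This stands: the point is inefficiency, not an error, and chance baseline imbalance does not make the planned comparison invalid.

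Three stronger readings are tempting, and the document supports none of them.

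- **That leaving out weeks 2 and 16 wastes precision on the main comparison.** It does not: the variance ratio for the week-28 contrast is 1.000 with complete data and about 0.99 with 10% dropout. Both visits follow directly on an intensive phase, when a short-term symptomatic effect may dominate, so keeping them out of the main neuroprotection contrast is defensible.
- **That adjustment lifts power to 82% or 86%.** Those figures need a score SD of 2.0 to 2.6 points, which conflicts with the broad entry criteria. The article also does not say whether SD 2 refers to change or to the score; if to the score, these power figures do not apply in general, although the variance ratio does.
- **That dropouts are a further loss on top of this.** Power at 13 per arm is already net of the 10% allowance. The article does not state how missing values are handled, which may be left to the analysis plan, and deletion of incomplete cases is only inferred from how the classical method works.

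What survives is the stated model itself: baseline as a time level, no covariate, and three levels that do not fit the slope comparison.

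**Conclusion.** The point holds as a modest improvement. Section 2.17 fixes an analysis that is less efficient than one using the same data. The variance ratio for the week-28 contrast is (1 + rho)/2, which is 0.75 to 0.95 over an assumed rho of 0.5 to 0.9. If SD 2 is the SD of change and the score SD is 5 points or more (assumed), the gain is about 0 to 2 power points on the 1.5-point early-versus-delayed contrast.

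Including baseline also cuts the expected group main effect to two thirds of its post-baseline average.

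Weeks 2 and 16 are worth at most about 1% of variance for the week-28 contrast. Their value lies in the slope comparisons of section 2.16, where they could reduce slope variance by about 15% (weeks 14–28) to 25% (weeks 0–28), but only if a straight line through visits that follow an intensive phase is credible. For weeks 14–28 the stated model has only the two end points.

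The planned 13 per arm and 60 in total reproduce and can stay.

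**What to change.** Replace the repeated-measures ANOVA for UPDRS with a mixed model for repeated measures on the post-baseline scores. Include arm, visit as a category, arm-by-visit, baseline UPDRS and baseline-by-visit, with an unstructured covariance, and use all randomised patients with any post-baseline value. Name the week-28 early-versus-delayed contrast as the comparison to be taken from it.

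Weeks 2 and 16 can be kept as categorical visits because they are already collected; this does not force them onto a straight line. For the slope comparisons in section 2.16, state separately which visits enter each slope and whether linearity is assumed.

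The cost is a few lines of text. The model runs in SPSS MIXED, and no visits or patients are added. Section 3 reports two patients enrolled, so the change can be made well before analysis.
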